### Statistical analysis

Data will be analysed on an intention-to-treat basis (primary outcome). Primary and secondary outcomes for the intervention and control groups will be compared.

Primary outcome: We expect that CCI will be skewed, so we will describe CCI as the median plus first and third quartiles. To test the hypothesis (H0) that the study arms result in similar CCIs (in other words, prehabilitation does not prevent postoperative complications), we will use a generalised linear model that can account for skewed data and zero inflation. The model will be adjusted for the minimisation factors used at randomisation. If no adequate model can be fit, the non-parametric Mann-Whitney U test will be used.

Secondary outcomes: All secondary outcomes will be described as means plus SD or median plus first and third quartiles for continuous data as appropriate. Categorical parameters will be described as frequencies plus percentage per time point. To account for repeat measurements of patients, we will use generalised linear mixed models to test the hypothesis of both study arms being equal in terms of secondary outcomes over time. Models will be adjusted for minimisation factors as well as baseline values (before randomisation) of the respective outcome.

Data distribution will be assessed by visual inspection of Q-Q plots.

As a secondary analysis, we will perform a PP analysis. Since the time between randomisation and surgery might differ between the two randomisation groups, we will additionally adjust generalised linear models of the primary outcome for this factor in a sensitivity analysis. Further, we will analyse the impact of adherence to the interventions to the primary outcome.

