Patient-reported measures of functional capacity remain notoriously unreliable. Better performance was seen when using the Duke Activity Status Index (DASI) questionnaire, which correlated well with objective, cardiopulmonary exercise testing (CPET)-derived parameters such as peak oxygen consumption (VO2_peak_) and was able to predict cardiovascular events in a recent trial.^14^ While CPET remains the gold standard for global assessment of functional capacity, it is laborious for the patient and costly. Therefore, the Canadian Cardiovascular Society recommends against performing perioperative CPET to enhance cardiac risk estimation.^15^ Nevertheless, an anaerobic threshold (AT) level of <11 mL/kg/min has been confirmed as a reliable predictor for increased perioperative risk.^16 17^ This also applies to the elderly patient.^18^ In addition, the AT has the better discriminatory power to identify patients with reduced functional capacity comparted to the 6 min walking test (6MWT), which is recommended for departments lacking CPET equipment.^19^ Very recent evidence found that an increased VE/VCO2 slope might be an even more sophisticated prognostic marker to predict morbidity in high-risk patients having major cancer surgery or patients undergoing lobectomy for lung cancer.^20 21^

With increasing age, the physiological resilience to external stressors such as surgery diminishes, while the number of comorbidities rises and muscle mass decreases. In addition, elderly people are often malnourished, have a weakened immune system and impaired wound healing. All these factors contribute to a reduction in functional capacity.^22^ Despite the inconsistency of the definition of frailty, it can be assessed using a variety of tools such as the clinical frailty scale or more objective Fried frailty criteria including gait speed and handgrip strength, which are useful predictors of all-cause mortality and cardiovascular disease and death in elderly surgical and non-surgical patients.^23–25^ Similarly, standardised screening and assessments exist for the diagnosis of malnutrition and sarcopenia, which demonstrated significant overlap with frailty.^26–28^ In summary, the elderly, frail, malnourished and sarcopenic patient is especially at risk for perioperative complications, however, many options for medical, physiological and psychological optimisation exist.^29^

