Potential reasons for these equivocal results are several fold, with the first and most important probably being inappropriate patient selection. From eight randomised trials addressing prehabilitation before major intra-abdominal cancer surgery, only two limited the study population to ‘high-risk’ patients, based on age, American Society of Anaesthesiologists or Dukes classification, however, none of them used objectively measured physical fitness as an inclusion criteria.^39^ Selecting patients with a relatively low risk for perioperative complications will inevitably lead to a dilution of the possible positive effects and produce negative results regardless of the intervention or surgeries studied. The small or inexistent benefit to ‘low-risk’ patients does not warrant the time-demanding and resource-demanding interventions. In addition, the time required for the intervention has been found to make recruitment of large cohorts difficult.^40 41^

Second, poor results may have been due to implementing unimodal rather than individually tailored multimodal interventions that cover all domains of patients’ health state prior to surgery, such as physical fitness, malnutrition, diabetes control, anaemia, smoking and psychological well-being.

Insufficient exercise capacity is believed to be the most important predictor for postoperative complications,^42^ and therefore, mandates careful assessment with appropriate patient selection. While physical fitness interventions (even high-intensity/interval training) have been proven to be safe and feasible and have led to a measurably increased fitness levels (e.g., 6MWT), they failed to produce outcome benefits, possibly due to inappropriate patient selection, unimodality (e.g., lack of considerations of other factors such as malnutrition) and adherence.^43–46^

Further, up to one-third of surgical patients are malnourished, and malnutrition has been proven to be associated with increased morbidity, mortality and cost.^47 48^ For malnourished patients, oral nutritional supplementation, in particular adequate protein supplementation, was shown to be effective in improving outcomes.^49–51^ Malnutrition is often associated with sarcopenia and frailty, making a combined intervention of exercise training and nutritional support promising.^22 45 52^ However, so far, nutritional assessment and intervention have been poorly standardised, making conclusions regarding its efficacy and interstudy comparisons difficult.^53^

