### Feasibility: preliminary data

After ethics approval and logistic preparations, we were able to include 18 patients from March 2022 to October 2022 (table 1).

**Table 1 T1:** Preliminary results

	Control group (n=8)	Intervention group (n=10)
Demographics/comorbidities		
Age (years)	78.25 (SD 5.4)	78.20 (SD 5.5)
Female sex	2 (25%)	1 (10%)
ASA score=III (n)	2 (25%)	2 (20%)
ASA score ≥IV (n)	6 (75%)	8 (80%)
Fried Frailty Scale (n)	1.9 (SD 1.1)	2.1 (SD 1.2)
Smoking (y/n)	1 (12.5%)	0 (0%)
Anaemia (y/n)	2 (25%)	4 (40%)
Nutritional deficit (NRS-2002≥3) (y/n)	2 (25%)	1 (10%)
Ischaemic heart disease or chronic heart failure (y/n)	4 (50%)	6 (60%)
Diabetes (y/n)	3 (37.5%)	3 (30%)
Obesity (BMI ≥30 kg/m^2^) (y/n)	1 (12.5%)	1 (10%)
Surgical procedure		
Cardiac	2	3
Orthopaedic	0	1
Thoracic	0	1
Urologic	3	4
Vascular	2	1
Visceral	1	0
Use of ECC (y/n)	2 (25%)	3 (30%)
P-POSSUM (baseline)	43.3 (SD 6.5)	45.2 (SD 8.2)
Days to surgery (days)	29.8 (SD 19.7)	28.5 (SD 9.3)
Laboratory parameters (baseline)		
Haemoglobin (g/L)	136.8 (SD 16.3)	126.9 (SD 13.8)
NT-proBNP (pg/mL)	3677.4 (SD 5022.3)	886.8 (SD 881.5)
Albumin (g/L)	33.3 (SD 3.9)	36.0 (SD 2.3)
Prealbumin (g/L)	0.22 (SD 0.04)	0.25 (SD 0.06)
HbA1c (%)	6.0 (SD 0.7)	6.4 (SD 1.4)
Creatinine (mmol/L)	147.9 (SD 51.5)	131.0 (SD 53.4)
Fitness		
MIP (cmH20)	51.3 (SD 28.0)	46.9 (SD 16.1)
AT (mL/min/kg)	9.8 (SD 1.0)	9.1 (SD 1.3)
VO2peak (mL/min/kg)	12.7 (SD 1.4)	11.8 (SD 2.8)
Questionnaires		
STAI (n)	10.6 (SD 2.4)	13 (SD3.9)
DASI (n)	4.1 (SD 0.8)	4.6 (SD 1.4)

ASA, American Society of Anesthesiologists; AT, anaerobic threshold; BMI, body mass index; DASI, Duke Activity Status Index; ECC, extracorporeal circulation; HbA1c, glycated haemoglobin; MIP, maximum inspiratory pressure; NRS-2002, Nutritional Risk Screening 2002; NT-proBNP, N-terminal-pro hormone brain-derived natriuretic peptide; STAI, state-trait anxiety inventory.

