### Inclusion criteria

Participants are eligible if aged 65 years or over, have planned major visceral, urologic, cardiac, vascular, orthopaedic or thoracic surgery, are classified as ASA III or higher by the attending anaesthetist, and have a proven deficit in functional capacity measured during the screening CPET defined as follows:

VO2 at AT <11 mL/kg/min or peak VO2 <14 mL/kg/min on cycle ergometer.VO2 at AT <13 mL/kg/min or peak VO2 <16.5 mL/kg/min on treadmill.VO2 at AT <9 mL/kg/min or peak VO2 <11.3 mL/kg/min with arm crank.VE/VCO2 slope ≥33 (independent of modality).

Patients with VO2 above thresholds during the screening CPET will nevertheless be consented, in order to collect their CCI at 30 days. CCI at 30 days will be compared descriptively between patients qualifying and not qualifying for this study for qualitative clinical assessment outside the purpose of this study.

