### Group allocation (minimisation)

After completion of the screening visit (CPET), patients who fulfil the inclusion criteria are randomised using computer-generated random numbers, into either intervention or control group. For group allocation, a probabilistic minimisation procedure is used to achieve balanced groups in regard to parameters known to be relevant for outcome after major surgery. We have included the following parameters in the minimisation algorithm (SecuTrial, V.6.1.1.10): type of surgery (visceral, urologic, cardiovascular, orthopaedic, thoracic), smoking, presence of anaemia (haemoglobin below 120 g/L in females, <130 g/L in males), nutritional deficit (NRS ≥3), age group (65–74, 75–84, 85+), ischaemic heart disease or heart failure, known diabetes, sex, obesity (body mass index (BMI) >30 kg/m^2^) and use of extracorporeal circulation.

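### The primary CCI model adjusts only for the categorical minimisation factors and omits baseline CPET fitness: a modest, avoidable loss of precision, not an error

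*Protocol article*

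**What the plan says.** The Statistical analysis section plans a generalised linear model for CCI that can handle skewness and excess zeros, and fixes its covariates: "The model will be adjusted for the minimisation factors used at randomisation". The fallback has no adjustment: "If no adequate model can be fit, the non-parametric Mann-Whitney U test will be used". The only further adjustment named for the primary outcome is a sensitivity analysis for the time from randomisation to surgery.

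Group allocation (minimisation) introduces its list with "We have included the following parameters in the minimisation algorithm". It names ten factors, each used as a category, for example "age group (65–74, 75–84, 85+), ischaemic heart disease or heart failure, known diabetes, sex, obesity". No CPET variable is among them.

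The Introduction gives fitness a leading role. Under Interventions to reduce perioperative risk: "Insufficient exercise capacity is believed to be the most important predictor for postoperative complications". Under Risk prediction before major surgery, a low anaerobic threshold (AT) "has been confirmed as a reliable predictor for increased perioperative risk", also in older patients, and the VE/VCO2 slope is described as possibly a better marker still. The Inclusion criteria require that patients "have a proven deficit in functional capacity measured during the screening CPET defined as follows", and allocation follows that test. A baseline CPET is therefore available before randomisation in every randomised patient.

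**The concern.** A covariate that predicts the outcome and is measured before randomisation can be added to the primary model at little cost. It removes explainable variation and corrects the estimate for chance differences between arms. The article identifies such a covariate, selects patients on it and measures it in all of them, but leaves it out of the primary analysis. At stake is some power and some protection against an unlucky split on fitness. The validity of the randomised comparison is not at stake.

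**Working it through.** **Inputs from Sample size:** control median CCI 30, IQR 21–37; 15% improvement, so 0.15 × 30 = 4.5 points; alpha 0.05 (sidedness not stated, two-sided assumed); power 0.80; 388 evaluable patients, 194 per arm.

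**Assumed:** ρ, the partial correlation of the baseline CPET variable with CCI given the minimisation factors. The article gives no value, so a range is shown. A linear model stands in for the planned skewed, zero-inflated one.

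**1. The stated sample size.** With a normal shape, SD = 16/1.349 = 11.86. A two-means calculation then gives 220 patients, or 232 to 256 after Wilcoxon efficiency factors of 0.955 or 0.864. The 388 is not reproduced. The internal CCI distribution is not shown, so 388 is not thereby proven wrong, and this point does not depend on it. Taking 80% power at 388 as given, the implied standardised effect is 2.802 × √(2/194) = 0.2845, and the implied SD is 4.5/0.2845 = 15.8. Both SDs are carried forward.

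**2. Gain from one CPET covariate.** Residual variance is multiplied by 1 − ρ², so effective N = 388/(1 − ρ²) and power = Φ(2.802/√(1 − ρ²) − 1.96).

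| ρ | Effective N | Power, calibrated to 80% | Power, SD 11.86 |
|---|---|---|---|
| 0 | 388 | 80.0% | 96.2% |
| 0.1 | 392 | 80.4% | 96.4% |
| 0.2 | 404 | 81.6% | 96.8% |
| 0.3 | 426 | 83.6% | 97.5% |

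**3. Range restriction.** Only patients with a deficit are randomised. As an illustration, keep the lowest 50% or 30% of a normal covariate. Its SD shrinks to u = 0.603 or 0.514 of the original. A correlation of 0.3 becomes 0.3u/√(1 − 0.09 + 0.09u²) = 0.19 or 0.16. Put into the power formula, these give about 81.4% and 81.0%. The restriction is not complete: if the listed criteria are alternatives, a patient can qualify on VE/VCO2 slope with AT above its cut-off, and the slope has no upper limit. Table 1 shows AT SDs of 1.0 and 1.3 mL/min/kg.

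**4. Chance imbalance.** The standard error of a standardised between-arm difference is √(2/194) = 0.10. An imbalance of 1.96 standard errors is 0.2 SD, exceeded in either direction about once in 20 trials. Unadjusted, it shifts the CCI difference by 0.2 × ρ × SD:

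- ρ = 0.1: 0.24 to 0.31 points
- ρ = 0.2: 0.47 to 0.63 points
- ρ = 0.3: 0.71 to 0.94 points, or 16% to 21% of 4.5

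A typical imbalance of one standard error at ρ = 0.3 shifts it by 0.36 to 0.48 points.

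**The case against.** The case against is strong on size.

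- **Nothing is wrong as it stands.** Adjusting for the minimisation factors is correct, and randomisation keeps the comparison valid without CPET. This stands. A reader might infer that the primary result would be biased, or that precision and protection against imbalance are lost altogether. The article supports neither: fitness is balanced in expectation, and only the increment beyond ten adjusted factors is forgone. Several of those factors, such as age, heart disease and nutritional risk, plausibly carry part of the fitness information.
- **The predictor statement is general.** It is worded as a belief and concerns surgical patients at large, not a group already selected for low fitness. This stands and points to the lower end of the range.
- **Table 1 proves nothing about imbalance.** A reader might take the AT difference in the first 18 patients (9.8 against 9.1, about 0.59 SD) as a sign that minimisation fails on fitness. With 8 and 10 patients the standard error is √(1/8 + 1/10) = 0.47 SD, so this is within chance. The markers also point in different directions: the control group has the higher AT but the far higher NT-proBNP.
- **The secondary models are no contradiction.** They adjust each measure for its own baseline; a postoperative complication index has none.
- **More terms could trigger the unadjusted fallback.** The ten factors already take 4 + 2 + 8 × 1 = 14 terms (five surgery types, three age bands, eight binary factors), possibly twice over in a two-part model. That one more would make the model fail is speculative.
- **The statistical analysis plan may add covariates.** It may, and that would settle the point. But the article states the primary covariate set outright, so this is a stated choice and not an omission.

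**Conclusion.** The point holds as a modest efficiency weakness. The primary model leaves out a continuous baseline measure that the article itself ranks as a leading predictor and that is available in every randomised patient. Under an assumed partial correlation of 0.1 to 0.3, the cost is about 0.4 to 3.6 percentage points of power from the stated 80%, with the lower end more likely. It is smaller still if the IQR-based SD is right, because power is then already about 96%. The 0.7 to 0.9 point shift describes an unlucky draw at the top of the assumed range, not an expected effect. All these figures rest on the assumed correlation and a linear approximation. The fact of the omission does not.

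**What to change.** Keep every minimisation factor and add one continuous baseline CPET covariate to the primary model, fixed before anyone sees unblinded outcome data. Two choices are workable:

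- VE/VCO2 slope, which the Inclusion criteria treat as independent of test modality. This is the simpler option.
- VO2 at AT, made comparable across cycle, treadmill and arm crank, since its eligibility thresholds differ (11, 13 and 9 mL/kg/min).

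Suggested wording: *The primary model will include all minimisation factors and, in addition, the chosen baseline CPET measure as a continuous covariate; a missing or undeterminable value will be replaced by simple imputation from baseline data, without regard to arm.*

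No new data are needed. The cost is one more term (two if it enters both parts of a two-part model) and the rule for undeterminable values. Adding baseline P-POSSUM, using age and haemoglobin as continuous values, or testing an arm-by-fitness interaction is optional and not needed to resolve this point.

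While this sentence is open, list the covariates by name: the Subgroup analysis section counts frailty score among the minimisation parameters, but Group allocation does not.

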### Sample size

Based on internal data (Bern University Hospital), median CCI is expected to be 30 (IQR 21–37). Assuming an average clinically relevant improvement of 15% in the intervention group compared with the control group, the sample size calculation for a non-parametric Wilcoxon-Mann-Whitney test resulted in a total patient sample of 388 (assuming a significance level alpha of 0.05 and power of 0.80). We expect a dropout rate of 20%. We, therefore, need 466 patients: 233 in each arm. We aim to complete the inclusion within 3 years.

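### The primary analysis can switch, with no objective or allocation-blind trigger, from a model adjusted for the minimisation factors to an unadjusted Mann-Whitney test

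*Protocol article*

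**What the plan says.** The protocol article, under Statistical analysis, expects a skewed CCI and states for the primary outcome: "we will use a generalised linear model that can account for skewed data and zero inflation". It continues: "The model will be adjusted for the minimisation factors used at randomisation". The factors are listed under Group allocation (minimisation): type of surgery, smoking, anaemia, nutritional deficit, age group, ischaemic heart disease or heart failure, diabetes, sex, obesity and use of extracorporeal circulation.

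Then comes the switch: "If no adequate model can be fit, the non-parametric Mann-Whitney U test will be used". The only diagnostic named in the section is this: "Data distribution will be assessed by visual inspection of Q-Q plots".

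The same section plans a sensitivity analysis that adds the time from randomisation to surgery to the GLM. Under Sample size, "the sample size calculation for a non-parametric Wilcoxon-Mann-Whitney test resulted in a total patient sample of 388".

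**The concern.** The switch is written into the plan; it is not a detail merely left out. Three features of it are weak.

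- **Trigger.** Adequacy of fit is judged on the primary outcome data, with no stated rule (non-convergence, a residual criterion, an information criterion) and no requirement that allocation be concealed at that moment. Reading a Q-Q plot is subjective.
- **Loss of adjustment.** A standard Mann-Whitney test takes no covariates. The fallback therefore discards the factors that the allocation was designed to balance, and its standard error no longer matches the design.
- **Change of question.** A GLM compares means, or a probability of zero together with a mean severity. The Mann-Whitney test concerns the probability that a patient in one arm has a lower score than a patient in the other. The time-to-surgery sensitivity analysis exists only for the GLM.

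At stake are the size and power of the primary test, and whether its result can be defended if the fallback is used.

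**Working it through.** **1. The plan's own figure.** 388 is stated for a Wilcoxon-Mann-Whitney test. The inputs are "median CCI is expected to be 30 (IQR 21–37"), a 15% improvement (0.15 × 30 = 4.5 points if applied to the median), alpha 0.05 and power 0.80. With SD = 16/1.349 = 11.86 and a two-sided test, Noether's formula gives 234 and other Wilcoxon variants give 230 to 254. So 388 is not reproduced from the stated inputs. It implies an SD of about 14.7 to 15.5, which is plausible for a skewed score. The step to 466 is 388 × 1.2 = 465.6. The point below does not depend on 388 being right; it takes the planned 80% power at face value.

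**2. Cost of dropping the adjustment.** Let R² be the share of outcome variance explained by the minimisation factors. The document gives no value, so it is assumed. If minimisation balances the factors almost fully, the true variance of the treatment difference is (1 − R²) times the variance that the unadjusted test uses. Put s = √(1 − R²). The planned non-centrality is 1.960 + 0.842 = 2.802. This is a large-sample approximation.

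- Unadjusted size = 2 × [1 − Φ(1.960/s)]
- Unadjusted power = Φ[(2.802 − 1.960)/s]
- Adjusted power = Φ(2.802/s − 1.960), at size 5%

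| Assumed R² | s | Unadjusted size | Unadjusted power | Adjusted power |
|---|---|---|---|---|
| 0.1 | 0.949 | 3.9% | 81% | 84% |
| 0.2 | 0.894 | 2.8% | 83% | 88% |
| 0.3 | 0.837 | 1.9% | 84% | 92% |

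At R² = 0.2: 1.960/0.894 = 2.191, giving size 2.8%; 0.842/0.894 = 0.941, giving 83%; 2.802/0.894 − 1.960 = 1.172, giving 88%.

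**3. Is the switch remote?** Entered as categories, the ten factors use 4 (surgery, five types) + 2 (age, three groups) + 8 (the other factors) = 14 parameters. If the chosen model has a separate zero part, and 10% of patients score zero (assumed), about 0.10 × 388 = 39 zeros would support 14 + 1 = 15 coefficients, or 39/15 = 2.6 zeros per coefficient. A fitting failure is then a realistic event.

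**4. Do the two analyses answer the same question?** Simulation: 194 per arm, 4,000 runs, no covariates. The assumed control distribution has quartiles 21/30/37, 10% zeros and an upper tail reaching 100. The Mann-Whitney test is compared with a joint 2-df test of a two-part model, which is one possible reading of the plan.

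| Scenario | Mann-Whitney rejects | Joint two-part test rejects |
|---|---|---|
| 15% scaling of scores | 87% | 85% |
| 4.5-point shift of non-zero scores | 82% | 67% |
| 15% of complications prevented outright | 65% | 91% |
| More zeros, non-zero scores 12% higher | 7% | 87% |

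Neither test is uniformly better, and they can disagree. The last row is a constructed extreme.

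**5. Type I error.** Under no effect each of these two tests alone holds about 5% (4.8% to 5.7% at 10% or 20% zeros). Taking the better of the two p-values gives 7.9% (10% zeros) and 8.3% (20% zeros). A rule that switched on residual misfit in 25% to 75% of simulated trials, with a robust-variance severity part, gave 5.1% to 6.1%.

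**The case against.** The strongest reply has four parts.

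*The model's family, link and contrast belong in a statistical analysis plan, which is not shown.* This is fair: their absence from a condensed article is no finding. But the article does state the switch and does state an unadjusted fallback, and those two choices can be judged as written.

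*The order is fixed: model first, Mann-Whitney only on failure of fit.* Correct. A reader might infer a type I error of 8% or more from the open choice. The text does not support that, because it does not allow selection on p-values. The 8% is an upper bound for result-driven choice between one pair of tests. Switching only on non-convergence, blind to allocation, would inflate far less. What remains is that the text requires neither.

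*The model may well have one treatment parameter.* A reader might infer that a model for zero inflation necessarily has two treatment effects with none designated. The document names no such model, and a Tweedie-type GLM handles zeros and skew with a single coefficient. The comparisons in steps 3 and 4 of the working therefore illustrate one reading only.

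*Sizing on Wilcoxon and analysing with an adjusted model is acceptable.* It is. A reader might take the sample size to be wrong because it was computed for the fallback, or might take the GLM to be underpowered. Neither follows. The power ordering depends on how the treatment works, and it reverses when complications are prevented outright.

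It can also be said that the unadjusted fallback errs on the safe side and stays above 80% power in the illustration. That is so, but it gives away power that the design has already paid for.

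**Conclusion.** The point holds in a limited form. As written, the primary analysis can move from an adjusted GLM to an unadjusted rank test on an undefined judgement of adequacy, without required blinding. If the fallback is used, the test is conservative and weaker: at an assumed R² of 0.2, size 2.8% and power 83%, against 5% and 88% with adjustment. Over R² from 0.1 to 0.3 the power loss runs from about 3 to 7 percentage points. These figures assume near-complete balance on the factors and a large-sample approximation.

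Some inflation of type I error from an outcome-dependent switch is possible, but its size under this rule cannot be fixed from the document. The simulated values rest on assumed CCI distributions, since only a median and quartiles are given. The documents do not support the claims that the planned model lacks a single treatment parameter or that the sample size was computed for the wrong test.

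**What to change.** Before unblinding, amend the primary analysis, in the protocol or the analysis plan, to do three things:

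1. Name one primary model and the one treatment contrast that tests the null hypothesis.
2. Allow the fallback only on an objective trigger, for example non-convergence under a stated fitting procedure, assessed and documented blind to allocation.
3. Replace the plain Mann-Whitney fallback with a covariate-adjusted rank-based analysis. A proportional-odds model for the ranked CCI, adjusted for the minimisation factors, would serve. It accommodates the zeros, the skew and the value 100 for death, and its unadjusted score test is the Wilcoxon test used for the sample size. The time-to-surgery sensitivity analysis can then be carried over by adding that covariate.

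The cost is a change of wording and slightly more analysis work. The fallback effect would be an odds ratio or a probability index, so medians by arm should be reported beside it. The proportional-odds model brings its own assumption. Whether it should replace the GLM as the primary model is a matter of preference, and this point does not require it.

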### Study hypothesis

We hypothesise that the implementation of a multimodal, multidisciplinary prehabilitation programme over 2–4 weeks, consisting of physical exercise, nutrition, anaemia correction and smoking cessation, will result in lower CCI within 30 days after major surgery in elderly patients.

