#### Safety outcomes

Days to surgery.(Serious) adverse events.

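### Adjusting the primary-outcome model for time from randomisation to surgery cannot check the robustness of the intention-to-treat effect if allocation changes that time

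*Protocol article*

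**What the plan says.** All places are in the protocol article.

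- Statistical analysis: "Data will be analysed on an intention-to-treat basis (primary outcome"), using a generalised linear model suited to skewed data with excess zeros. "The model will be adjusted for the minimisation factors used at randomisation". Time to surgery is not in this model.
- Same section, on the added analysis: "we will additionally adjust generalised linear models of the primary outcome for this factor in a sensitivity analysis". The factor meant is the interval from allocation to the operation, and the reason offered for including it is: "Since the time between randomisation and surgery might differ between the two randomisation groups".
- Group allocation (minimisation): "After completion of the screening visit (CPET), patients who fulfil the inclusion criteria are randomised using computer-generated random numbers". The interval therefore starts at allocation and ends at an event after it.
- Study hypothesis: the intervention is a "multidisciplinary prehabilitation programme over 2–4 weeks". Only one arm receives it, and it takes place within that interval.
- Safety outcomes: the first item is "Days to surgery".

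The article gives no separate estimand, such as a direct effect, for the adjusted model and no assumptions under which its result should be read.

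**The concern.** A chance imbalance in a baseline factor is a good reason to adjust. A systematic difference between arms in a quantity that begins at randomisation is a consequence of allocation. The reason the protocol gives for adjusting is therefore the condition under which adjusting can mislead. It can do so in two ways.

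1. If the interval itself affects complications, holding it fixed removes part of the total effect that the intention-to-treat analysis is meant to estimate.
2. If unmeasured severity affects both the interval and complications, conditioning on the interval creates an association between arm and severity that randomisation had removed. The article makes such a link plausible: the Introduction says organ-specific treatment must be finished before major surgery, and the Control group section allows abnormal findings to be treated first.

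At stake is how a secondary result is read. A reader would take agreement between the two models as support and disagreement as a warning, and neither reading would be justified.

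**Working it through.** The plan states no figure for this sensitivity analysis, so there is none to reproduce. The check asks what the adjusted model would return.

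**Inputs from the article.** Sample size section: median CCI 30, IQR 21 to 37, improvement 15%. Taken as a shift, 0.15 × 30 = 4.5 points. If CCI were normal, its SD would be (37 − 21)/1.349 = 11.9. Table 1: days to surgery 29.8 (SD 19.7, n = 8) in control and 28.5 (SD 9.3, n = 10) in intervention.

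**Model (linear, for illustration).** Let a be the days by which the arm shifts the interval, b the CCI points per day of interval, g the days per SD of unmeasured severity, c the CCI points per SD of severity, and V the within-arm variance of the interval. The slope of CCI on the interval within arm is

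k = b + c·g/V,

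and the arm coefficient after adjustment is

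total effect − a·k.

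The coefficient is unchanged only if a = 0 or k = 0.

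**Assumed set 1.** Within-arm SD of the interval 7 days (V = 49); correlation of severity with the interval 0.6, so g = 4.2; c = 0 or 3; b = 0 or −0.2; total effect −4.5. When both paths act, k = −0.2 + 3 × 4.2/49 = −0.2 + 0.257 = 0.057.

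| Active path | k | a = 0 | a = 3 days | a = 7 days |
|---|---|---|---|---|
| Neither | 0 | −4.50 | −4.50 | −4.50 |
| Interval affects CCI | −0.200 | −4.50 | −3.90 | −3.10 |
| Severity affects CCI | 0.257 | −4.50 | −5.27 | −6.30 |
| Both | 0.057 | −4.50 | −4.67 | −4.90 |

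A simulation with 2,000,000 patients per scenario agrees to within 0.03 points, and the model without the interval returns about −4.5 throughout. When both paths act, the direct effect (total − b·a) is −3.90 for a = 3 and −3.10 for a = 7. The adjusted values match neither the total nor the direct effect.

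**Assumed set 2, with stronger confounding.** g = 6 days, c = 6 points, residual SD of the interval 7 days, b = 0. Then V = 36 + 49 = 85 and k = 36/85 = 0.424.

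- a = 3: shift −1.27 points (28% of 4.5)
- a = 5: shift −2.12 points (47%)
- a = 7: shift −2.96 points (66%)

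If sicker patients are operated on sooner, g changes sign and so do these shifts: +1.27, +2.12 and +2.96.

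**Sensitivity of set 2 to the spread of the interval.** The pooled pilot variance is (7 × 19.7² + 9 × 9.3²)/16 = 218, an SD of 14.8 days. With V = 218, k = 36/218 = 0.165, and a 5-day shift moves the estimate by 0.83 points (18% of 4.5).

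**What the pilot says about a.** Intervention minus control is 28.5 − 29.8 = −1.3 days, with standard error √(19.7²/8 + 9.3²/10) = 7.6 (p = 0.87). It neither supports nor excludes a shift of 3 to 7 days.

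**The case against.** The strongest reply is that harm is conditional and may be absent. The article says only that the interval might differ. Under Participants and enrolment, at least 2 weeks before surgery are required of every patient before consent is sought, so the programme may fit into time that was already scheduled. If the arm does not move the interval, adjustment does no harm. The analysis is also labelled a sensitivity analysis and decides nothing.

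All of this stands, and it rules out three stronger readings that a reader might infer.

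- **That the adjustment does bias the result.** It can. Bias needs the arm to shift the interval and the interval, or a common cause, to relate to CCI.
- **That extra waiting is part of the programme, so the adjusted estimate will favour prehabilitation.** No passage says surgery is postponed in the intervention arm, and the direction depends on which path dominates and on whether sicker patients wait longer or shorter.
- **That about half of the planned effect is at risk.** The 47% in set 2 leaves out any effect of the interval itself, and its 6 points per SD of severity is about half the implied CCI SD of 11.9, left over after adjustment for the minimisation factors. It falls to 18% with the pooled pilot SD. In set 1 with both paths acting, the shift is 0.17 to 0.40 points, or 4% to 9%.

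One part of the reply fails. If the arm does not shift the interval, the adjustment is harmless but has also lost its stated reason. If the arm does shift it, the result cannot be read as a robustness check.

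**Conclusion.** The point holds as a modest one. The planned sensitivity analysis conditions on a variable that allocation may change, and the protocol lists days to surgery as an outcome. If allocation shifts the interval and the interval or severity relates to CCI, the adjusted coefficient has a different target from the intention-to-treat effect.

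The documents fix neither size nor direction. The assumed inputs give shifts from near zero to about 2 to 3 CCI points in either direction. These figures come from a linear sketch on the CCI scale, not from the planned model for skewed, zero-inflated data.

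Two readings are assumed: that the interval is the observed one, and that the safety outcome and the Table 1 row refer to essentially that interval, since the article does not define where days to surgery starts. The primary analysis and the sample size are not affected.

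**What to change.** - Remove the adjustment for time from randomisation to surgery as a sensitivity analysis of the treatment effect.
- Report days to surgery by arm, as its place among the safety outcomes already implies, and define its start and end points.
- If the interval is of interest, use the planned interval recorded before randomisation, either as a baseline covariate or in an interaction with arm.
- If the observed interval is still to be analysed against CCI, label that analysis as exploratory mediation and state its assumptions, above all that no unmeasured common cause of interval and complications remains.

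The cost is a change of wording and, for the third item, recording the scheduled surgery date before allocation where one exists. The article confirms only that at least 2 weeks are available, so a date may be missing for some patients. No change to sample size or to the primary analysis is needed.
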